### Patient Recruitment

Patients will be recruited from 9 medical institutions in Japan (Textbox 1). Attending physicians will conduct recruitment during patients’ regular outpatient consultations. The recruitment period will run from February 8, 2024, to July 30, 2024.

Participating institutions: 11 medical centers in Japan.The University of Tokyo HospitalMitsui Memorial HospitalMeiji Yasuda Life Insurance Company Tokyo HospitalKobe University HospitalAkita University HospitalTokai University HospitalOkayama Saiseikai General HospitalSawaki Internal Medicine and Diabetes ClinicYokota Medical ClinicAikawa Comprehensive Internal Medicine ClinicYokohama Rosai Hospital

To detect a 0.3% difference in the primary outcome (change in HbA_1c_), assuming an SD of 0.41% (the average observed in 2 prior studies [17,61]), and to achieve a 2-sided significance level of .05 with 80% statistical power, the minimum required sample size is 31 patients per group. Considering an estimated dropout rate of approximately 10%, we aim to recruit a total of 70 patients (35 in the intervention group and 35 in the control group).

All participants will receive a comprehensive written and verbal explanation before providing written informed consent. Eligibility screening will be conducted only after consent is obtained. If any findings related to efficacy or safety arise during the trial that may impact patient consent, we will promptly disclose this information to participants and obtain renewed consent.

We will use survey instruments as part of the inclusion and exclusion criteria (Textbox 2). To recruit patients who are both likely to benefit and capable of participating, we will include only those meeting all inclusion criteria (Textbox 3) while ensuring they do not meet any exclusion criteria (Textbox 4), following the methods of a prior study [62]. We anticipate a roughly equal sex distribution and an average participant age in the late 50s. Women undergoing menopausal transition will be included if they meet the study’s criteria.

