During the study, we will not restrict the use of supplements or drinks that may affect blood glucose and blood pressure. In both the intervention and control groups, T2D treatment—including oral T2D medications, insulin, glucagon-like peptide 1 receptor agonists, and medication dosage—may be adjusted at the discretion of the attending physician. We will collect information on T2D-related medication and medications affecting sleep at E1, E3, and E4.

Discontinuation is defined as a patient expressing a decision to withdraw or failing to record data for a continuous period of 7 or more days. If a participant discontinues during the intervention period, we will attempt to collect E3 measurement items. If discontinuation occurs during the observation period, we will attempt to collect E4 measurement items.

**Table 4 table4:** Study events—1 measurement period and 4 visits spanning approximately 26 weeks.

Event	Focus	Time	Key activities
E0	Physical baseline assessments and initial registration	Enrollment: ≥7 days before the beginning of the intervention	Collect consent Collect demographic information: age, sex, date of type 2 diabetes diagnosis, smoking and drinking habits, macrovascular disease, diabetic retinopathy, periodontal disease, tinea pedis, diabetic neuropathy, and other medical history Collect physical data: hemoglobin levels, albumin, uric acid, blood urea nitrogen, estimated glomerular filtration rate, creatinine, fasting blood glucose, HbA_1c_^a^, low-density lipoprotein cholesterol, high-density lipoprotein cholesterol, triglycerides, urine specific gravity, urinary protein, urine albumin-to-creatinine ratio, height, body weight, and blood pressure measurements Collect medication status Conduct screening surveys (STOP-J^b^, ISI-J^c^, IRLSQ-J version 2.2^d^, AUDIT-C-J^e^, PHQ-8-J^f^, and TTM^g^ Sleep Questionnaire) Conduct PSQI-J^h^ survey Distribute actigraph (iAide2) and run-in period diary
Run-in	Baseline	From E0 for 2 weeks	Patients record daily bedtime and risetime, with automated (blinded) measurements of sleep parameters and step count

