### Outcome Measures

#### Primary Outcome

The primary outcome of this study is the between-group difference in the change in HbA_1c_ from baseline (E0) to either the end of the intervention period at week 12 (E3) or, for patients who discontinue before E3, the point of discontinuation. A reduction of 0.3 percentage points in HbA_1c_ is considered clinically significant [75,76].

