### Statistical Analysis

In this study, we define 3 analysis populations: the full analysis set (FAS), the per-protocol set (PPS), and the safety analysis set (SAS). The FAS includes all patients for whom the primary outcome was obtained. Following the intention-to-treat principle, we will analyze data based on the assigned group in the FAS analysis. The PPS consists of the FAS population, excluding patients who violated eligibility criteria after randomization, had 7 or more contiguous days of nonuse of the iAide2, or took medications affecting sleep. The SAS includes all patients who used the iAide2 at least once after randomization. In the safety analysis using the SAS, we will analyze data based on the intervention actually used by patients, regardless of allocation. The FAS will serve as the primary analysis population, while the PPS will provide supportive results. All safety analyses will be conducted using the SAS.

Patient characteristics will be presented as mean, SD, minimum, 25th percentile, median, 75th percentile, and maximum for continuous variables, and as frequency and proportion for categorical variables.

In the primary analysis, we will compare the change in HbA_1c_ from baseline (E0) to week 12 (E3; or the point of discontinuation, if earlier) between groups using analysis of covariance, with baseline HbA_1c_ (ie, HbA_1c_ at E0) included as a covariate in the FAS. For participants who discontinue the study, the most recent HbA_1c_ measurement before E3 will be used.

We will also conduct 2 subgroup analyses: one based on baseline HbA_1c_ at E0 (<8.5% or ≥8.5%) and the other based on age at initial registration (E0; <65 or ≥65 years). Subgroup analyses of the primary outcome will be performed in each analysis set to assess whether the efficacy of BedTime is consistent across these subgroups.

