## Results

Recruitment began on February 8, 2024, and ended on August 29, 2024. The intervention period concluded on December 6, 2024, and the observation period ended on February 26, 2025, with 70 participants completing the observation period (Figure 4). The analysis is currently underway, and we anticipate publishing the results in July 2025. Before commencing analysis, we will conduct a thorough review of all collected data and data entry.

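### A 7-day recording gap counts as discontinuation, so the primary analysis as written can replace a measured week-12 HbA1c with an earlier value

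*Protocol article*

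**What the plan says.** All references are to the protocol article.

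- **Intervention Process** defines discontinuation as a stated wish to withdraw, or "failing to record data for a continuous period of 7 or more days". It then adds: "If a participant discontinues during the intervention period, we will attempt to collect E3 measurement items".
- **Primary Outcome** measures the HbA1c change from E0 to week 12 (E3) or, "for patients who discontinue before E3, the point of discontinuation".
- **Statistical Analysis** repeats this in the analysis of covariance and adds: "For participants who discontinue the study, the most recent HbA_1c_ measurement before E3 will be used". It says the full analysis set (FAS) follows intention to treat and defines it so: "The FAS includes all patients for whom the primary outcome was obtained". It also removes patients with 7 or more consecutive days without the iAide2 from the per-protocol set (PPS). The discontinuation clause is applied to several week-24 (E4) analyses as well.
- **Table 4** lists HbA1c at E0, E3 and E4. None is listed at E1 or E2.
- **Results** reports the trial "with 70 participants completing the observation period".

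**The concern.** A recording gap is a lapse in adherence. It is not loss to follow-up, and a patient can have one and still give blood at week 12. The article gives no narrower definition of discontinuation, so the substitution rule reaches these patients. The rule asks for a value from before E3, which on its face excludes the E3 value that the team has tried to collect.

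Two things are at stake. First, the endpoint is no longer HbA1c at week 12 for everyone, because how well a patient records data decides which measurement counts. That conflicts with the stated intention-to-treat principle. Second, the estimate is pulled toward whatever the earlier value shows. If that value is the baseline, the patient contributes no change at all.

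**Working it through.** **1. Which value the rule selects.** Take a patient with an 8-day gap in week 5 who attends E3.

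- By the definition in Intervention Process, this patient has discontinued.
- By Primary Outcome, the endpoint is taken at the point of discontinuation. By Statistical Analysis, it is the latest HbA1c before E3.
- By Table 4, the only scheduled HbA1c before E3 is E0, so change = E0 − E0 = 0.
- If the E3 items were instead drawn when the patient stopped, the value is a real measurement, taken at about week 5 and analysed as week 12.

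On either path the observed E3 value is not the one used.

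**2. The plan's own sample size.** Inputs from Patient Recruitment: "To detect a 0.3% difference in the primary outcome (change in HbA_1c_), assuming an SD of 0.41" percentage points, and "2-sided significance level of .05 with 80% statistical power, the minimum required sample size is 31 patients per group".

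- Normal approximation: n = 2 × [0.41 × (1.960 + 0.842) / 0.3]² = 29.3, so 30 per arm.
- Two-sample t test (noncentral t): 30.3, so 31 per arm. This matches the plan.
- Dropout of about 10%: 31 / 0.9 = 34.4, so 35 per arm and 70 in total. This also matches.
- Power with 35 per arm and every week-12 value used: 85.5%.

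The sample size is not in error.

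**3. Illustration if E0 is carried forward.** Let a share d of each arm have its change set to 0. Assume a mean change of 0 in control and a true difference of 0.30.

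- Expected difference = 0.30 × (1 − d).
- Control variance = (1 − d) × 0.41². Intervention variance = (1 − d) × 0.41² + d(1 − d) × 0.30². The mixture SD is the square root of their average.
- At d = 0.10: difference 0.27; variances 0.1513 and 0.1594; mixture SD 0.394.

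Power is for a two-sample t test with 35 per arm:

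| d | Difference | Power, mixture SD | Power, SD fixed at 0.41 |
|---|---|---|---|
| 0 | 0.300 | 85.5% | 85.5% |
| 5% | 0.285 | 83.2% | 81.8% |
| 10% | 0.270 | 80.7% | 77.5% |
| 20% | 0.240 | 74.8% | 67.5% |
| 30% | 0.210 | 68.0% | 56.1% |

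Only the 10% row uses a figure from the document, and that figure is a planned dropout rate, not a rate of recording gaps. The other rows show the range. For comparison, leaving 10% of each arm out of the analysis altogether gives 81.5% power with the difference still at 0.30. At that share the main cost is therefore bias in the estimate rather than loss of power.

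**The case against.** **The rule may be meant more narrowly, with an early-stop sample.** Statistical Analysis speaks of leaving the study, and the promise to seek E3 items could mean a sample taken at that moment. The FAS definition points the same way. Every patient has an E0 HbA1c, because a value of 7.5% or more is an entry criterion. If E0 could serve as the outcome, no one could lack it and the FAS restriction would exclude nobody. A reader might infer from Table 4 that the change is always set to zero, but the documents do not support that. It is zero only if E0 is the value carried forward. What remains is that an earlier measurement would still stand in for week 12.

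**The 7-day clause cannot be meant mechanically.** All equipment and diaries are collected at E3, so taken literally every patient would discontinue early in the observation period, yet 70 are reported as completing it. Nonuse of the iAide2 is also handled separately, as a PPS exclusion. These are fair signs of a looser intent, but the article gives no other definition and does not say which value applies to a patient who lapses and then attends E3.

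**Seventy of 70 completed.** This makes true withdrawals few or none, so redefining the FAS or specifying an elaborate imputation would matter little. It does not exclude 7-day gaps, whose number is not given. It also suggests that week-12 values exist for nearly everyone, so the rule would mostly displace real data.

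**Bias between arms.** A reader might infer that the rule favours BedTime, because only the intervention arm is asked to reply after a missed Event press (Table 1). If 20% of controls and 5% of intervention patients were carried forward during a common fall of 0.2 to 0.4 points, the spurious difference would be 0.15 × 0.2 = 0.03 to 0.15 × 0.4 = 0.06. None of those inputs has a source in the article. The device records passively in both arms, and both arms receive diary reminders and low-battery messages. Imbalance is possible but not shown, and its direction is open. With equal shares the bias is toward no difference.

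**Conclusion.** The point holds as a defect in the primary endpoint as written. The definition of discontinuation, the substitution rule and the continued collection of E3 items do not fit together. Followed literally, they let a recording lapse replace an observed week-12 HbA1c within an intention-to-treat analysis.

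The size is uncertain and probably modest. If E0 were carried forward in 10% of each arm, a true 0.30 would be estimated as 0.27, below the 0.3 points that the article treats as clinically significant. Power would be about 81% or 78%, depending on the SD, which is close to the 80% target. These figures assume equal shares in both arms, no mean change in control and E0 as the value used. An early-stop sample would generally dilute the effect less. The article does not support a claim that change is near zero for all such patients, that a large share is affected, or that the comparison is tilted toward one arm.

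**What to change.** - In Primary Outcome and Statistical Analysis, state that the primary analysis uses the HbA1c observed at E3 for every randomised patient who has one, whatever their recording gaps or early stopping.
- Remove from the primary analysis both the alternative endpoint at discontinuation and the rule that takes the latest value before E3.
- Let recording gaps affect PPS membership only.
- Apply the same principle to the E4 analyses, where the gap definition cannot work once the equipment has been returned.
- Name a missing-data method for any E3 value that is truly absent. With 70 completers it should seldom be needed.
- Keep the carry-forward version as a sensitivity analysis, and report by arm how many patients it changes.

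No new data are required. The cost is a late change to the primary endpoint wording. Under Ethical Approval, protocol amendments go to the review board. Results describes the analysis as under way but also says a data review comes before it. The change should therefore be dated, documented and made before the group comparison is finalised, with a statement of what was known about outcomes by arm at that time.

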In the secondary analysis, changes in HbA_1c_ at week 12 (E3) and week 24 (E4) will be analyzed using the same approach as in the primary analysis. The proportion of patients with HbA_1c_ below 7% at E3 and E4 (or at the point of discontinuation, if earlier) will be compared between groups using the Fisher exact test. Changes from baseline in step counts, various laboratory test values, and questionnaire scores at E3 and E4 (or at the point of discontinuation, if earlier) will also be analyzed as key endpoints. Changes in T2D medications, categorized as weakened, unchanged, or strengthened, will be compared between groups using the Cochran-Mantel-Haenszel test. The proportion of newly added medications will be compared between groups using the Fisher exact test. A paired (2-sample) *t* test will be used for within-group comparisons of changes in TPB Questionnaire measurements over weeks 0 (E1), 10 (E2), 12 (E3), and 24 (E4). Changes in TPB Questionnaire and SRB Questionnaire measurements between week 12 (E3) and week 24 (E4) will be compared using a *t* test. A paired *t* test will also be used for within-group comparisons from week 0 (E1) to week 12 (E3) for goal achievement rate, goal increment rate, goal reduction rate, average number of coping strategies implemented per day, and the number of identified barriers.

As an exploratory analysis, we will use linear regression to examine the relationship between the average number of coping strategies implemented per day and improvement in HbA_1c_ within the intervention group. The model will include the average number of coping strategies implemented per day and baseline HbA_1c_ as explanatory variables, with the change in HbA_1c_ as the response variable. Changes from baseline to week 12 (E3) and week 24 (E4) (or the point of discontinuation, if earlier) will be assessed.

We will perform a statistical analysis of safety outcomes by calculating the frequency, number of cases, and percentage of individuals experiencing adverse events during the trial, intervention, and observation periods. For the intervention and observation periods, data will be compiled separately for each group, and the percentages will be compared between groups using the Fisher exact test.

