We selected the HbA_1c_ level as our primary outcome, as it is recognized as a global standard for assessing glycemic control and an appropriate indicator of T2D treatment effectiveness [77]. According to the Japan Diabetes Society’s treatment guidelines, patients with T2D should aim to lower their HbA_1c_ level below 7% to prevent complications [78]. Therefore, in addition to analyzing absolute changes in HbA_1c_ levels, we examined the proportion of patients achieving an HbA_1c_ level below 7%. We acknowledge that T2D duration may influence the primary outcome. Although our recruitment process does not explicitly stratify participants by disease duration, this information is collected at registration and will be incorporated into the analysis to account for its potential impact on study outcomes.

In this study, we have chosen a “formidable” control [79], using the same devices as the intervention group. As an initial proof-of-concept study, our goal is to determine whether our specific behavior change intervention is more effective than simply having patients record their bedtime and risetime. Evidence suggests that providing patients with a pedometer can increase their activity levels [80], raising concerns that bedtime and risetime recording in the control group may similarly trigger behavioral changes, potentially making it more challenging to demonstrate the intervention’s superiority statistically. By providing the control group with a diary but withholding the intervention functionality, we have designed the study to offer strong evidence of the intervention’s effectiveness—should it indeed be effective.

Many behavior interventions demonstrate solid short-term gains that later fade [39]. This study includes a 12-week observation period following the intervention to assess whether the benefits persist or diminish. Behavior change maintenance is theorized to result from active, ongoing self-regulation, with habit formation emerging after a period of successfully regulating a new behavior [81]. Our goal is to foster sustainable behavior change, ensuring that the new pattern becomes an enduring habit.

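### The unadjusted Fisher test for HbA1c below 7% is very conservative with the few responders expected; a baseline-adjusted Firth logistic model would recover power and correct near-threshold imbalance

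*Protocol article*

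**What the plan says.** All places are in the protocol article.

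- **Statistical Analysis, secondary analysis.** The rule for HbA1c below 7% at E3 and E4 is that responder proportions "or at the point of discontinuation, if earlier) will be compared between groups using the Fisher exact test". No covariate or stratum is named.
- **Statistical Analysis, primary analysis.** The change in HbA1c is compared "using analysis of covariance, with baseline HbA_1c_ (ie, HbA_1c_ at E0) included as a covariate in the FAS". The secondary analyses of HbA1c change at E3 and E4 take the same approach.
- **Study inclusion criteria.** Baseline HbA1c must be 7.5% or higher.
- **Patient Recruitment.** Allocation is 1:1 by minimisation. HbA1c enters as two levels, cut at 8.5%, alongside age, sex and institution. The sample size is set "To detect a 0.3% difference in the primary outcome" with an SD of 0.41 percentage points.
- **Discussion.** Beside absolute change, and with reference to the national treatment target, "we examined the proportion of patients achieving an HbA_1c_ level below 7" per cent.

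The article gives no expected response rate and no power for this proportion, and Table 5 does not list it among the secondary outcomes.

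**The concern.** The entry limit and the responder threshold are half a percentage point apart, while the planned effect is 0.3. Only patients who start close to 7.5% have much chance of finishing below 7%. Two consequences follow.

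First, responders will be few. An exact test on sparse counts can reject at the 5% level only for a few extreme tables, so its real error rate falls far below 5% and power goes with it.

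Second, the number of near-threshold patients in each arm affects the raw result. Minimisation balances patients below 8.5% as a block but not who within that block starts at 7.6% rather than 8.3%. The plan uses baseline HbA1c to deal with this for the continuous change and leaves it out for the responder comparison.

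At stake is a secondary result tied to the guideline target. A real difference is more likely to be missed than the data require, and the reported difference in proportions may carry some chance imbalance.

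**Working it through.** **1. The plan's own figure.** The inputs are an effect of 0.3, an SD of 0.41 and "2-sided significance level of .05 with 80% statistical power". The normal formula gives n = 2 × (1.960 + 0.842)² × 0.41² / 0.3² = 29.3, so 30 per arm. The noncentral t gives power 79.6% at 30 and 80.9% at 31, which matches "the minimum required sample size is 31 patients per group". Allowing for dropout, 31 / 0.9 = 34.4, so 35 per arm and 70 in total. The stated size is reproduced. At 35 per arm the continuous comparison has about 86% power.

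**2. Chance of finishing below 7%.** With mean fall d this is Φ((7 − baseline + d) / 0.41).

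| Baseline | d = 0.3 | d = 0 |
|---|---|---|
| 7.5 | Φ(−0.49) = 31% | Φ(−1.22) = 11% |
| 7.8 | Φ(−1.22) = 11% | Φ(−1.95) = 2.6% |
| 8.0 | Φ(−1.71) = 4% | Φ(−2.44) = 0.7% |
| 8.5 | Φ(−2.93) = 0.2% | about 0% |

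**3. What Fisher needs.** With 35 per arm and no control responders, the two-sided p-value for k intervention responders is 2 × C(35,k) / C(70,k).

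- k = 5: p = 0.054.
- k = 6: p = 0.025.

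So at least 6 v 0 is needed. An unadjusted Pearson chi-square already rejects at 4 v 0 (z = 0.114 / 0.0555 = 2.06, p = 0.039).

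**4. Power.** The documents give no baseline distribution. The assumption is 7.5% plus an exponential excess with mean 0.5, 0.8 or 1.2, a common fall of 0 or 0.2 in both arms, SD 0.41 and effect 0.3. The response probability per arm is the formula in step 2 averaged over baseline. Fisher and chi-square power follow by adding up binomial probabilities over all tables with p < 0.05. The Firth column (arm plus continuous baseline, penalised likelihood ratio test) comes from 2,500 simulated trials per row.

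| Common fall | Mean excess | Expected responders, control v intervention | Fisher | Chi-square, unadjusted | Firth with baseline |
|---|---|---|---|---|---|
| 0 | 0.5 | 1.1 v 4.0 | 8.0% | 26.3% | 21.3% |
| 0 | 0.8 | 0.8 v 2.8 | 2.9% | 16.2% | 12.3% |
| 0 | 1.2 | 0.6 v 2.0 | 0.9% | 8.6% | 7.4% |
| 0.2 | 0.5 | 2.7 v 7.4 | 23.6% | 36.8% | 37.6% |
| 0.2 | 0.8 | 1.9 v 5.4 | 13.0% | 28.9% | 27.0% |
| 0.2 | 1.2 | 1.4 v 3.9 | 6.2% | 21.4% | 18.4% |

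Relative to Firth, Fisher loses between (37.6 − 23.6) / 37.6 = 37% and (7.4 − 0.9) / 7.4 = 88% of the power. With no effect, Fisher rejects in 0-0.8% of trials, Firth in 0.5-2.7% and chi-square in 0.3-5.4%. A separate simulation with the arms balanced at 8.5% gave 1-25% for Fisher and 7-36% for Firth.

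**5. Which part is due to baseline.** The unadjusted chi-square does about as well as the adjusted model, so the gap is mainly Fisher's conservatism. Large-sample logistic models with and without baseline isolate the covariate. The efficiency ratio is 1.06 to 1.28, worth at most about 5 power points at 35 per arm (for example 16.7% to 17.6%, or 28.7% to 32.6%). In the small-sample rows with no common fall, adjustment shows no gain over chi-square.

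**6. Remaining imbalance.** Under the assumed baselines, 82-95% of responders start below 8.0% at SD 0.41 (58-83% at SD 0.8). With arms balanced at 8.5% only:

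- The share starting below 8.0% differs between arms by about 8 percentage points on average.
- The arms differ by 4 or more such patients in about 25-34% of trials, and by 6 or more in about 7-14%.
- In one scenario (mean excess 0.8, common fall 0.2, effect 0.3), the raw risk difference averaged about 12 points when the intervention arm had at least 4 extra such patients, and about 7 when the control arm did.

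**7. Sensitivity to SD.** At SD 0.7, Fisher has about 5-16% power and Firth 13-21%.

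**The case against.** The strongest reply is that nothing here is wrong. Fisher's test controls type I error, is a standard choice for sparse tables, and serves a secondary companion to a continuous analysis that is already adjusted for baseline and has about 86% power. Chance imbalance is also already allowed for in a valid test. All of that stands. It is why the point is an improvement and not a defect.

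Three stronger readings are tempting, and the documents do not support them.

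- **That leaving out baseline HbA1c throws away most of the power.** Setting Fisher against adjusted Firth changes two things at once. Once the type of test is separated from the covariate, baseline accounts for about 0-5 points.
- **That minimisation does nothing for the patients who can respond.** At SD 0.41 at least 99% of responders start below 8.5%, and that stratum is a balancing factor. Only imbalance inside it remains.
- **That a better test would make this endpoint informative.** Power stays below 40% in every row of the table.

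The reply also notes that the baseline distribution, common fall and response rates are assumptions. That is correct, and the sizes should be read as ranges.

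**Conclusion.** The point holds as a low-severity improvement. With the article's own entry limit, effect and SD, the Fisher test would run at an actual type I error below 1% and give up roughly a third to most of the power that the same data allow. The main cause is the test's conservatism with few events. Baseline adjustment adds little power, and its value is in correcting near-threshold imbalance within the stratum below 8.5%.

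The figures depend on assumed baseline distributions and 35 patients per arm, and the gap narrows as the SD grows. The direction is more secure than the size: Fisher was lower in every scenario examined. The primary analysis and its sample size are unaffected.

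**What to change.** In the secondary analysis, replace the Fisher comparison of HbA1c below 7% at E3 and E4 with Firth (bias-reduced) logistic regression containing arm and continuous baseline HbA1c. Report the baseline-standardised risk difference with its 95% confidence interval, and keep the Fisher test as an unadjusted sensitivity analysis. Switching only to an unadjusted chi-square would recover most of the power. It would not correct imbalance, however, and its error rate can slightly exceed 5% here (5.4% in one row).

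The Results section reports that follow-up is complete and analysis in progress. If outcome data have already been seen, the model should be labelled supportive and not presented as pre-specified.

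The cost is one sentence of analysis text and a standard routine. No new data are needed, since baseline HbA1c is collected at E0. The downside is a p-value that rests on a model and is no longer exact.
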